## Abstract

**Introduction::**

Acne vulgaris is a chronic inflammatory disease of the sebaceous glands that occurs in adolescent men and women. In recent years, the incidence of acne has increased year by year, so it is of great significance to find a precise and effective treatment and further explore its possible mechanism of action. The purpose of this study will be to explore a treatment method that has both traditional Chinese medicine characteristics and significant effects, and provides a higher level of evidence for acupuncture for acne vulgaris. It also provides patients with more treatment options.

**Methods/design::**

The study will be a randomized controlled trial divided into 2 parallel groups. This pragmatic randomized controlled trial will recruit 66 patients who are diagnosed with acne vulgaris. 30-minutes acupuncture sessions will be provided to patients assigned to the intervention group. All participants will continue to receive conventional treatment. The selection of outcomes will be evaluated by the skin lesions score scale.

**Discussion::**

This trial may provide evidence regarding the clinical effectiveness, safety, and cost-effectiveness of acupuncture for patients with acne vulgaris.

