As for the treatment of acne vulgaris, mild acne is usually treated with topical drug smears, and moderate or severe acne is mostly treated with topical drug smears combined with antibiotics and retinoic acid drugs.^[9,10]^ Due to the long period of treatment for moderate to severe acne, patients need to take antibiotics for a long time, which greatly increases the incidence of adverse reactions such as nausea, vomiting, and dizziness, and it is easy to relapse after stopping the drug. TCM treats acne and adopts the principle of syndrome differentiation and treatment. Starting from the cause, the advantages are significant. Acupuncture, as a unique method of treating diseases in TCM, has the function of “internal disease and external treatment,” and can treat systemic diseases through the conduction of meridians and acupoints. In this study, the efficacy of acupuncture in the treatment of acne vulgaris will be observed through the establishment of commonly used western medicines as controls and clinical randomized controlled trials. We aim to explore the clinical efficacy of acupuncture in the treatment of acne and provide guidance for future clinical work and research work.

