### Interventions

2.3

The intervention group and the control group were treated according to the following schemes, respectively. At the same time, the 2 groups of patients should be cleaned daily, gentle facial cleanser to wash excess facial oil, and avoid direct sunlight.

Control group: The control group will be given topical AA cream. After instructing the patient to clean the face by themselves, use a clean cotton swab to apply an appropriate amount of vitamin A acid cream to the redness and swelling of the skin, and apply it once a day before going to bed at night. The total course of treatment is 4 weeks.

Intervention group: Patients in the intervention group will be given the same treatment measures as those in the control group, while undergoing acupuncture treatment. Differentiated acupoints and local points of skin lesions will be used. The syndrome of wind-heat will be taken from *Hegu, Quchi, Chize, Weizhong, Feishu, Fengmen*, and Damp-heat syndrome will be taken from *Hegu, Quchi, Zusanli, Sanyinjiao and Yinlingquan*. The patients are going to be placed in the lateral position, and the acupoints were routinely disinfected with 75% ethanol. The chest, abdomen and limbs were acupunctured with a 1.5-inch needle, and the face was punctured with a 1-inch needle. The needle-needle method is used to lift the needle, and the needle is twisted and twisted. Based on the patient's local feeling of soreness and numbness, the needle will be left for 30 minutes, and the needles are going to be given every 10 minutes during this period. Acupuncture treatment is once every other day, 10 treatments are 1 course, and 3 courses are treated.

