#### Primary outcome measures

2.4.1

We will use the skin lesions score scale as the primary outcome indicator. This scoring table was developed in accordance with the guidelines of the latest version of the “Guidelines for Clinical Research of New Chinese Medicines.” This score sheet is an evaluation index for the main symptoms of acne, and comprehensively evaluates the main efficacy of each treatment plan. The scoring items of the scoring table are to evaluate the amount and distribution of skin lesions such as pimples, nodules, and cysts. There are 4 main items to be scored, namely the type of skin lesions, the number of skin lesions, the degree of swelling and rupture, and the color of the skin lesions. Each item is divided into 4 severity levels, which are rated as 0 points, 2 points, 4 points, and 6 points in turn, and the total score is finally calculated.

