#### Secondary outcome measures

2.4.2

We will use the systemic symptom recording scale as the secondary outcome measure. This record scoring table is based on TCM-related symptoms of acne. It reflects the changes in the symptoms of acne patients after various treatments, and it is of auxiliary evaluation significance. Evaluation content includes complexion, emotion, urination, stool, sleep, appetite, menstruation (female patients only), etc. The score is divided into 2 levels, which is 0 for normal and 1 for abnormal. The above 2 scoring tables were evaluated every 2 weeks before and during the treatment, that is, a total of 3 evaluations. Observe the therapeutic effect of each treatment scheme on the condition of acne as a whole.

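### The abstract offers evidence on safety and cost-effectiveness, but neither defined outcome measures cost and none is a safety outcome

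*Protocol article*

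**What the plan says.** The abstract closes with a statement of scope: "This trial may provide evidence regarding the clinical effectiveness, safety, and cost-effectiveness of acupuncture for patients with acne vulgaris".

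The outcomes are set out in Section 2.4. For the primary outcome (2.4.1): "We will use the skin lesions score scale as the primary outcome indicator". For the secondary outcome (2.4.2), in the singular: "We will use the systemic symptom recording scale as the secondary outcome measure". The first scale grades lesion type, number, swelling and colour. The second scores items such as sleep, appetite, mood and bowel function as normal or abnormal.

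Harms enter the methods in Section 2.2.4 only. Patients with severe adverse reactions or treatment accidents are listed under the elimination, shedding and abort criteria. The same section asks researchers to record why participation stopped, how that relates to the trial, and the evaluation indicators at that time.

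On the comparison, the Introduction says that "the efficacy of acupuncture in the treatment of acne vulgaris will be observed through the establishment of commonly used western medicines as controls". Section 2.3 defines the arms. Control: "The control group will be given topical AA cream". Intervention: "Patients in the intervention group will be given the same treatment measures as those in the control group, while undergoing acupuncture treatment". The abstract's methods paragraph agrees: "All participants will continue to receive conventional treatment".

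**The concern.** A trial can report only on what it plans to measure. The abstract names three kinds of evidence, and the outcome section serves one of them. If the plan is followed as written, there will be no data from which to judge cost-effectiveness. What can be said about safety will come from discontinuation records that were not set up as an outcome.

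The placing of harms adds to the safety problem. Severe reactions are a route out of the trial, not a result to be compared between arms. If safety were later summarised only in patients who were kept, the severe reactions would be missing from the summary because of the criterion itself. Non-severe reactions are not mentioned at all.

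A smaller matter concerns the aim. The Introduction describes western medicine as the control without saying that the acupuncture arm receives it too. The sentence is not false, but it leaves the estimated effect less clear than Section 2.3 does.

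**Working it through.** No figure in the plan needs reproducing. The check sets the claimed scope beside what is defined.

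| Evidence named in the abstract | Outcome in 2.4 | Analysis in 2.7 | Elsewhere in the article |
|---|---|---|---|
| Clinical effectiveness | Lesion score; symptom scale | Tests listed by type of data | Aims in the abstract and Introduction |
| Safety | None | None named | 2.2.4: severe reactions as a criterion; reasons for stopping recorded |
| Cost-effectiveness | None | None named | Nothing |

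**Step 1, cost.** Two outcomes are named; the number concerning cost, resource use or utility is 0. A 0/1 symptom checklist is not described as a utility measure. Section 2.7 lists t tests, analysis of variance, chi-square and rank-sum tests, and no economic analysis. The term occurs once, in the abstract.

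**Step 2, safety.** Of the same two outcomes, the number defined as safety outcomes is 0. The symptom scale is presented as an auxiliary measure of therapeutic effect. The chi-square test for counts in 2.7 could be applied to adverse events, but no such count is defined. The adverse reactions mentioned in the Introduction are background on long-term antibiotics, not trial data.

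**Step 3, effect of the elimination criterion.** Section 2.2.4 does not say which listed patients leave the analysis and which only stop treatment. If those with severe reactions are removed, the number of severe reactions among those retained is 0 in each arm, whatever the true rate. A usable safety count therefore needs all treated patients in the denominator.

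**Step 4, what a safety table could show.** The article gives 30 or 33 patients per arm. With no events among n patients, the one-sided 95% upper limit for the event rate is 1 − 0.05^(1/n). For n = 30 this is 1 − 0.905 = 9.5%. For n = 33 it is 1 − 0.913 = 8.7%. A clean table would still be compatible with a rate near 9%, so a safety result here can only be descriptive.

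**Step 5, the contrast.** Control is cream. Intervention is cream plus acupuncture. The difference between arms estimates what acupuncture adds to the cream.

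**The case against.** The strongest reply is that a journal article condenses the full protocol. Adverse-event procedures are commonly left to that document, and the schedule in Figure 1 is not shown. This stands as far as procedures go, and no fault is found with their absence. The point is a mismatch within the article: it lists its outcomes explicitly and claims a wider scope than they cover.

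A second reply is that the sentence is hedged (it says only that the trial may provide evidence) and sits in the abstract's discussion. The aims stated in the abstract and Introduction concern effect and clinical efficacy only. That is fair, and it keeps the point modest: cost-effectiveness is a claim about scope, not a declared objective. But a hedge covers an uncertain result, not a quantity that nobody measures.

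A reader might also infer four stronger things that the article does not support:

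- *That no harms data will exist.* Section 2.2.4 records reasons for stopping and their relation to the trial, so some will.
- *That the trial promises acupuncture against the drug.* The control arm does receive a western medicine alone, so the Introduction's sentence is literally true. The add-on design is stated openly in the abstract and in Section 2.3.
- *That the arms differ by 30 clinic contacts when outcomes are measured.* Three courses of 10 sessions do make 30. But three evaluations two weeks apart end at week 4 if the first is at baseline, and sessions every other day give about 28 / 2 = 14 by then.
- *That the trial is open-label.* Section 2.6 has blinding in its heading but says nothing about who is blinded. No sham is described, so patients would probably know their arm; whether assessors are blinded is not stated.

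**Conclusion.** The point holds for the scope claim. Cost-effectiveness is unsupported: one claim, no measure and no analysis. Safety is weakly supported: no defined outcome, with partial records limited to discontinuations and severe reactions. Effectiveness is the only one of the three with outcomes behind it.

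This should be corrected, but it is a limited defect. It changes what the trial may conclude and leaves the randomisation, the primary outcome, the type I error and the power as they are. The comparator wording in the Introduction is a minor clarification, not an error.

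The conclusion assumes that the outcome list in Section 2.4 is complete. If the full protocol defines adverse events as an outcome, the safety part reduces to adding that outcome to the article. The cost part would fall only if the full protocol contained an economic measure of which the article gives no sign.

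**What to change.** 1. In the abstract's Discussion paragraph, delete cost-effectiveness.
2. For safety, choose one of two courses. Either delete the word as well, or add adverse events by arm to Section 2.4.2 as a descriptive secondary outcome. If added, count them in all treated patients, including those eliminated under Section 2.2.4, and say that no formal comparison is intended. This concerns counting and reporting only; it does not touch who stops treatment.
3. In the Introduction, state the aim as the effect of adding acupuncture to the topical cream compared with the cream alone, in line with the abstract's methods paragraph and Section 2.3.

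The cost is a few words, a narrower claim and, if safety is kept, one descriptive table with the recording of non-severe reactions that it needs. Section 2.9 says that recruitment has not begun and that ethics review is still to come, so on the article's own account the change can be made before any patient is enrolled.

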**Trial registration number::**

CTR2000030427

## Introduction

1

Acne vulgaris is a chronic inflammatory disease of the sebaceous glands that occurs in adolescent men and women.^[1]^ Its occurrence is related to the gonad endocrine function in the human body. Once this function loses normal regulation, it will form chronic recurrent inflammation in the hair follicles and sebaceous glands of the human face.^[2]^ Acne vulgaris appears as acne, pimples, nodules, or cysts. According to relevant research data, the incidence of acne is about 20%, and nearly half of them occur in adolescents. In some regions, the incidence of adolescents exceeds 90%.^[3,4]^ Generally speaking, the incidence of men will not be lower than that of women. However, because women pay more attention to skin care, female patients often seek medical treatment in clinical investigations. With the improvement of living standards and economic conditions, people's requirements for beauty are getting higher and higher, and personal appearance is more and more important.^[5]^ Therefore, the prevention and treatment of acne is an urgent need of adolescents. Acne is a chronic inflammation in the type of pathological changes, and its lesions are in the hair follicles and secreting strong sebaceous glands.^[6]^ However, the most prone areas are the face and chest and back of the human body, because these areas are the areas where sebum secretion is more active. Acne develops further and can produce skin lesions like blackheads, pimples, cysts, and nodules.^[7,8]^ There is no name for acne in the classics of Chinese medicine, but there are many other names that are consistent with the pathology of acne. Generally speaking, these disease names are named according to the location of the disease and the characteristics of the skin lesions. For example, there are different disease names such as facial sores and acne. These disease names on the one hand reflect that the affected area of acne is generally on the face, and also reflect that the susceptible population of acne vulgaris is adolescents. According to the pathogenesis characteristics of the disease and the law of the development of the disease, traditional Chinese medicine (TCM) holds that the main pathogenesis of acne vulgaris is the accumulation of lung and stomach fever, or excessive thinking, discord between qi and blood, or imbalance of responsibility.

As for the treatment of acne vulgaris, mild acne is usually treated with topical drug smears, and moderate or severe acne is mostly treated with topical drug smears combined with antibiotics and retinoic acid drugs.^[9,10]^ Due to the long period of treatment for moderate to severe acne, patients need to take antibiotics for a long time, which greatly increases the incidence of adverse reactions such as nausea, vomiting, and dizziness, and it is easy to relapse after stopping the drug. TCM treats acne and adopts the principle of syndrome differentiation and treatment. Starting from the cause, the advantages are significant. Acupuncture, as a unique method of treating diseases in TCM, has the function of “internal disease and external treatment,” and can treat systemic diseases through the conduction of meridians and acupoints. In this study, the efficacy of acupuncture in the treatment of acne vulgaris will be observed through the establishment of commonly used western medicines as controls and clinical randomized controlled trials. We aim to explore the clinical efficacy of acupuncture in the treatment of acne and provide guidance for future clinical work and research work.

## Methods/design

2

### Study design and settings

2.1

The study will be a randomized controlled trial divided into 2 parallel groups. This protocol is based on the Standard Protocol Project: Recommended Guidelines for Interventional Trials. If they agree, they will sign an informed consent form. Following the schedule described in Figure 1, only participants who read and agreed to the agreement and signed informed consent will be allowed to participate in the study. After patients were included in this clinical observation, the research guidelines of randomized controlled trials will be strictly followed, and the randomized number table method are going to be used to divide the admitted patients into test groups and control groups on average.

**Figure 1 F1:**
[figure not shown]
SPIRIT figure for the schedule of enrollment, interventions, and assessments. Abbreviations: SSRC = systemic symptom recording scale, SPIRIT = Standard Protocol Items: Recommendations for Interventional Trials, TCM = traditional Chinese medicine.

### Participants

2.2

All patients with acne vulgaris included in this clinical study will be recruited at the Third People's Hospital of Ningxia (Ningxia, China) acupuncture clinic and dermatology clinic. Case recruitment is initially scheduled for July 2020 to July 2021, with a total of 60 cases included (Fig. 2).

**Figure 2 F2:**
[figure not shown]
Study design flow chart.

#### Diagnostic criteria

2.2.1

The diagnostic criteria for western medicine used in this clinical research project are strictly in accordance with the relevant descriptions in the textbook “*Clinical Dermatology*” (editor: Zhao Zhan). The main points of diagnosis are as follows:

① The age of onset is young people, male, or female. The most prone areas are the cheeks and forehead, followed by some areas with strong sebum secretion, such as the front chest, back, and shoulders.② The lesions show skin-like changes, usually pimples, blackheads, acne, knots, nodules, cysts, and scars. These skin lesions are generally symmetrical in the affected area, and are usually accompanied by strong sebum secretion, a slow and persistent condition.

Acne Severity Grading Standards: The acne grading standards used in this clinical research project are derived from the grading standards established by Pillsbury. The classification criteria are as follows:

① Grade I (mild): most of the types of skin lesions are blackheads, which do not appear intensively or intermittently, and are accompanied by a small amount of inflammatory pimples.② Grade II (moderate): most of the types of skin lesions are acne. The lesions are mainly concentrated on the face, accompanied by a moderate number of pimples and acne that may develop further.③ Grade III (Severe): the type of skin lesions is mainly inflammatory pimples and acne. The main lesions are on the face, neck, chest, and back, with a small number of nodules (less than 3). The number is around 51 to 100.④ Grade IV (severe): the type of skin lesions is mainly inflammatory pimples that may develop further, accompanied by more nodules and cysts (greater than 3), the number of skin lesions is greater than 100, and the probability is greater scar.

#### Inclusion criteria

2.2.2

① Patients who meet the above-mentioned diagnostic criteria for acne vulgaris; aged between 16 and 40 years; the severity of acne reaches grade II or above.② Did not take any drugs related to the treatment of acne within 1 month before receiving this clinical research protocol.③ Do not take antibiotics, glucocorticoids or retinoic acid drugs within 2 weeks.④ I have not received any other topical medications related to acne within a week.⑤ Those who have no objection to the informed consent of this clinical research trial and agree to be observed and signed the informed consent form.

#### Exclusion criteria

2.2.3

Patients will be excluded if they meet the following criteria:

① The incidence of acne is classified as patients with nodular acne, agglomerated acne, scarring acne, fulminant acne, and premenstrual acne.② During the observation period of this clinical study, patients who are unavoidably exposed to direct sunlight or receive high-intensity ultraviolet rays are unavoidable.③ Acne caused by long-term exposure to specific chemicals or acne caused by long-term use of glucocorticoids.④ Those who are allergic or scarred, and patients who disagree with the treatment plan used in this clinical research.⑤ Patients with severe cardiovascular and cerebrovascular diseases, cardiopulmonary insufficiency, liver and kidney dysfunction, and severe infections;⑥ Women during pregnancy or lactation.

#### Elimination, shedding, and abort test criteria

2.2.4

Researchers participating in clinical trials should carefully record the reasons for the suspension of the trial and the relationship with the clinical trial. It is necessary to clearly record the unwillingness of the subjects to continue the clinical trials, put forward the reasons for withdrawing from the clinical trials, and record the evaluation indicators at the time of discontinuation in detail.

① Patients with incomplete data due to various reasons during the clinical observation process, which could not accurately determine the curative effect.② Patients who withdrew from the clinical observation treatment plan or did not cooperate with staff during the treatment for various reasons.③ Patients with severe adverse reactions or treatment accidents during the treatment process of this clinical observation.④ Patients who used other treatments related to acne without consent during the treatment process of this clinical observation.

### Interventions

2.3

The intervention group and the control group were treated according to the following schemes, respectively. At the same time, the 2 groups of patients should be cleaned daily, gentle facial cleanser to wash excess facial oil, and avoid direct sunlight.

Control group: The control group will be given topical AA cream. After instructing the patient to clean the face by themselves, use a clean cotton swab to apply an appropriate amount of vitamin A acid cream to the redness and swelling of the skin, and apply it once a day before going to bed at night. The total course of treatment is 4 weeks.

Intervention group: Patients in the intervention group will be given the same treatment measures as those in the control group, while undergoing acupuncture treatment. Differentiated acupoints and local points of skin lesions will be used. The syndrome of wind-heat will be taken from *Hegu, Quchi, Chize, Weizhong, Feishu, Fengmen*, and Damp-heat syndrome will be taken from *Hegu, Quchi, Zusanli, Sanyinjiao and Yinlingquan*. The patients are going to be placed in the lateral position, and the acupoints were routinely disinfected with 75% ethanol. The chest, abdomen and limbs were acupunctured with a 1.5-inch needle, and the face was punctured with a 1-inch needle. The needle-needle method is used to lift the needle, and the needle is twisted and twisted. Based on the patient's local feeling of soreness and numbness, the needle will be left for 30 minutes, and the needles are going to be given every 10 minutes during this period. Acupuncture treatment is once every other day, 10 treatments are 1 course, and 3 courses are treated.

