### Statistical analysis.

2.7

SPSS for windows 24.0 statistical analysis software will be used for calculation, and normality test and homogeneity test of variance will be performed on each group of data. For measurement data in which the data conforms to the normal distribution, we will use the mean ± standard deviation. For non-normally distributed measurement data, the median ± quartile interval is used. General data comparison between the 2 groups using independent sample *t* test. Comparisons before and after treatment will be performed using *t* test for paired data. One-way analysis of variance will be used for comparison between groups. X^2^ test will be used for count data, and nonparametric rank sum test will be used for rank data. All statistical tests are two-sided. *P* < .05 indicates a significant difference.

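### The stated 30 alternate-day acupuncture sessions run to day 59, but three two-weekly evaluations end around week 4 (week 6 at most), so the primary score is last read part-way through the course

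*Protocol article*

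**What the plan says.** All references are to the protocol article.

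- **Acupuncture dose (section 2.3, intervention group):** "Acupuncture treatment is once every other day, 10 treatments are 1 course, and 3 courses are treated".
- **Cream (section 2.3, control group):** "The total course of treatment is 4 weeks". The intervention arm also receives the cream: "Patients in the intervention group will be given the same treatment measures as those in the control group, while undergoing acupuncture treatment".
- **Evaluations (section 2.4.2, covering both the primary and the secondary scale):** "The above 2 scoring tables were evaluated every 2 weeks before and during the treatment, that is, a total of 3 evaluations".
- **Purpose of the primary score (section 2.4.1):** it "comprehensively evaluates the main efficacy of each treatment plan". That section names no time point.
- **Analysis (section 2.7):** "Comparisons before and after treatment will be performed using" a paired t test.

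Figure 1 is captioned "SPIRIT figure for the schedule of enrollment, interventions, and assessments" but is not shown in the text available. No visit week is printed anywhere in that text.

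**The concern.** The evaluation schedule fits a four-week treatment period, whereas the acupuncture schedule takes more than eight weeks. Taken literally, patients in the acupuncture arm attend many sessions after the last time anyone scores their skin.

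Two things are at stake. First, the primary result would be reported as the efficacy of the acupuncture plan when it describes only part of that plan, and any benefit or loss of benefit over the remaining sessions would go unmeasured. Second, section 2.7 plans a comparison of scores before and after treatment, but the visible text gives the acupuncture arm no reading after its treatment ends.

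The timing does not bias the comparison between arms. Both arms are scored at the same times and use the same cream. The issue is what that comparison measures.

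**Working it through.** **Inputs.** One session every other day, 10 per course and 3 courses (section 2.3); a cream course of 4 weeks (section 2.3); two-week spacing and 3 evaluations in total (section 2.4.2).

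**The plan's own figure.** Evaluations every 2 weeks over 4 weeks, counting the one before treatment: 4/2 + 1 = 3, at weeks 0, 2 and 4. The stated total is reproduced for a four-week treatment period.

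**Length of the acupuncture course.** Sessions: 3 × 10 = 30. With the first on day 1, session k falls on day 1 + 2(k − 1):

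- 10th session: day 19
- 20th session: day 39
- 30th session: day 1 + 2 × 29 = day 59, and 59/7 = 8.4 weeks

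Two-weekly evaluation across this course would need weeks 0, 2, 4, 6 and 8, which is five, plus one on or after day 59. The plan gives three.

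**Sessions completed at the last evaluation.** The number done by day d is (d + 1)/2, rounded down. Week 4 may be counted as day 28 or 29, and week 6 as day 42 or 43.

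| Reading of the three evaluations | Last evaluation | Sessions done | Share of 30 | Still to come |
|---|---|---|---|---|
| Weeks 0, 2, 4 (most natural) | day 28 / 29 | 14 / 15 | 46.7% / 50.0% | 16 / 15 |
| Weeks 2, 4, 6 after a separate baseline (less natural) | day 42 / 43 | 21 / 22 | 70.0% / 73.3% | 9 / 8 |

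**Sensitivity to rest between courses.** No rest is stated. A 7-day rest, assumed for illustration, would move the last session to day 59 + 2 × 7 = 73. The share done would fall to 11/30 (37%) by week 4 and 18/30 (60%) by week 6. Any rest widens the gap.

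**The case against.** The strongest reply is that the error lies in the session count and not in the evaluations. The four-week cream course and the three two-weekly evaluations agree with each other, and only the three courses of acupuncture depart from them. In a roughly translated text, a slip in the number of courses is plausible. If four weeks is the real treatment period, the primary score is read at the end of treatment and the harm described above disappears. This is a fair point, and it determines which remedy applies. It does not remove the contradiction: only 14-15 alternate-day sessions fit into four weeks, so the dose in section 2.3 would then be wrong. The four-week sentence also stands under the control group and need not govern acupuncture.

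A second reply is that Figure 1 may show a later visit. It may, but section 2.4.2 fixes the total at three, so a later visit would contradict that total and one of the two would need correcting.

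A third is that the week-6 reading is strained, since three evaluations after a separate baseline make four readings. I agree that week 4, with 47-50% of sessions done, is the better-supported figure. Week 6 is kept only to show that the conclusion does not depend on the choice.

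Finally, the paired test can still be computed on the last available score. That is true, but the result would be a mid-course change labelled as a post-treatment one.

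**Conclusion.** The concern holds. Two rules stated in the protocol article conflict. Thirty alternate-day sessions cannot finish before day 59, and three evaluations two weeks apart stop at week 4 on the natural reading, or at week 6 at the latest. The primary score is therefore last read after 47-50% of the stated acupuncture (70-73% on the less natural reading), with 15-16 sessions (or 8-9) still to come.

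This assumes a first session on day 1, no rest between courses and evaluation weeks inferred from the text. Rest between courses would only lower the percentages. The between-arm comparison remains unbiased by timing, but as written it answers a question about a partial course. This should be fixed before the trial starts.

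**What to change.** Decide which schedule is intended, and align the acupuncture course, the evaluations and the primary time point.

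- **(a) If four weeks of treatment is intended:** correct the acupuncture to 14-15 alternate-day sessions and name week 4 as the primary time point in both arms. If the session count is a drafting slip, this is a wording change. Otherwise it cuts the dose from 30 sessions to 14-15, which is for the investigators to decide.
- **(b) If 30 sessions are intended:** set one primary time point for both arms after the last session, at about week 9 from randomisation, and correct the total number of evaluations in section 2.4.2. State also whether the cream continues in both arms to that point. If it does not, days 29-59 may be without cream in both arms. This is only a possibility, because the abstract says "All participants will continue to receive conventional treatment" without saying what that treatment is or how long it lasts. The cost is two to three extra scoring visits (for example weeks 6 and 9, or 6, 8 and 9), about five more weeks of follow-up in both arms (week 9 instead of week 4), and more cream if it is continued.
- **If neither is changed:** limit the conclusion to the effect part-way through the acupuncture course, and do not describe the last score as a post-treatment value in that arm.

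Section 2.9 says that no patient has yet been recruited, so either correction can still apply to every participant.
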